.

# ABBREVIATIONS and ACRONYMS

UMSP: Uganda Malaria Surveillance Project

MoH: Ugandan Ministry of Health

EANMAT: East African Network for Monitoring Antimalarial Therapy

CQ: Chloroquine

AQ: Amodiaquine

AS: Artesunate

SP: Sulphadoxine pyrimethamene

US: United States

UCSF: University of California San Francisco

WHO: World Health Organisation

ACPR: Adequate clinical and parasitological response

ETF: Early treatment failure

LCF: Late clinical failure

LPF: Late parasitological failure

IMCI: Integrated Management of Childhood Illness

Hb: Haemoglobin

DHPS: Dihydropterate synthetase

DHFR: Dihydrofolate reductase

IRB: Institutional Review Board

DNA: Deoxyribonucleic acid

GCP: Good Clinical Practice.

# 1.0 STUDY SUMMARY

| **Title** | **Comparison of amodiaquine + artesunate and artemether + lumefantrine for treatment of uncomplicated malaria in Uganda: evaluation of efficacy, safety, and tolerability** |
| --- | --- |
| **Description** | Randomised, single-blinded trial |
| **Participants and sample size** | Ugandans aged > 6 months recruited from 4 study sites  Total sample size 1600 subjects, 400 per site  (2 treatment arms at each site with 200 subjects per treatment arm) |
| **Clinical Sites** | The study will be conducted at 4 of Uganda Malaria Surveillance Project (UMSP) sentinel sites namely, Tororo, Kanungu, Mubende and Arua. |
| **Selection Criteria** | 1. Not previously enrolled in this study 2. Age **1 – 10 years** 3. Weight > 10 kg 4. Fever (> 37.5ºC axillary) or history of fever in the previous 24 hours 5. Absence of any history of serious side effects to study medications 6. No evidence of a concomitant febrile illness 7. Provision of informed consent and agreement to follow-up for 28 days 8. No evidence of severe malaria or danger signs 9. Absence of repeated vomiting of study medications on day 0 10. *P. falciparum* mono-infection 11. Parasite density > 2000/ul and < 200,000/ul |
| **Study intervention** | Subjects will be randomized to treatment with amodiaquine + artesunate (AQ+AS) or artemether + lumefantrine (coartemether). Subjects in the AQ+AS arm will also receive placebo tablets to ensure that the number of doses received is identical in the two treatment groups. Subjects requiring repeat therapy (second-line therapy given for symptomatic malaria) will receive quinine. |
| **Follow-up** | Subjects will be followed for 28 days and will be asked to return for follow-up assessment on days 1, 2, 3, 7, 14, 21, 28, and any unscheduled day that they feel ill. |
| **Primary outcome** | Risk of clinical rescue therapy (second-line therapy given for symptomatic malaria) |
| **Secondary outcomes** | 1. Risk of clinical treatment failure (due to recrudescence) 2. Risk of parasitological rescue therapy 3. Risk of parasitological treatment failure 4. Risk of fever on days 1-3 5. Risk of parasitemia on days 2 and 3 6. Change in mean haemoglobin between days 0 and 28, or day of treatment failure 7. Proportion of patients with gametocytaemia during follow-up 8. Risk of serious adverse events during follow-up 9. Risk of adverse events of moderate or greater severity, at least possibly related to the study medications, excluding patients requiring rescue therapy |

# 2.0 INTRODUCTION

## 2.1 Background

Malaria remains one of the most serious global health problems and a leading cause of morbidity and mortality in Uganda. Appropriate case management, focusing on prompt treatment with effective antimalarial drugs, is the foundation of malaria control throughout sub-Saharan Africa. For decades, chloroquine (CQ) was the mainstay of antimalarial therapy, but the emergence of *P. falciparum* resistance to CQ has challenged control efforts.[1] The spread of CQ resistance has coincided with increased malaria-related morbidity and mortality in Africa, highlighting the urgent need to change antimalarial treatment policy in the face of rising CQ resistance.[2] However, the optimal replacement to CQ has not been clear and available alternatives are limited. In 2000, the Ugandan Ministry of Health (MoH) re-evaluated the national antimalarial drug policy in response to expanding CQ resistance. The combination of CQ plus sulfadoxine-pyrimethamine (CQ+SP) was chosen to replace CQ as first-line treatment for uncomplicated malaria. However, at the time that this decision was made, the efficacy and safety of the CQ+SP combination had not been evaluated in Uganda.

In 2002, the Uganda Malaria Surveillance Project (UMSP), a collaboration involving the MoH and academic partners, was formed to collect data on antimalarial therapies to aid the MoH in drug policy decision-making. A multi-site study was conducted at 7 sentinel sites in Uganda in 2002-2004 to compare the efficacy and safety of CQ+SP to potential alternatives for first-line therapy, including amodiaquine + SP (AQ+SP), and amodiaquine + artesunate (AQ+AS). Data from this study and a trial comparing the same combination regimens in Kampala are presented below in Table 1.(UMSP, unpublished data)[3] In summary, the risk of treatment failure with CQ+SP was unacceptably high at all sites. Treatment with AQ+SP or AQ+AS greatly reduced the risk of rescue therapy (for recrudescence or new infection) and the risk of true treatment failure compared to CQ+SP. Comparing the AQ-containing regimens, the risk of true treatment failure was lower with AQ+AS, but this was offset by a higher risk of new infection. Overall, AQ+SP lowered the risk of rescue therapy, especially at the sites with the highest transmission intensity.

**Table 1. Ugandan drug efficacy studies (2002-04): 28-day treatment outcomes in children less than 5 years**

| **Site** | **CQ+SP** | **AQ+SP** | **AQ+AS** |
| --- | --- | --- | --- |
| **Risk of Clinical Rescue Therapy*** | | | |
| Kanungu | 86% | 53% | - |
| Mubende | 70% | 44% | - |
| Kyenjojo | 70% | 35% | - |
| Kampala | 45% | 20% | 16% |
| Jinja | 57% | 19% | 19% |
| Tororo | 75% | 45% | 55% |
| Apac | 32% | 17% | 28% |
| **Risk of Clinical Treatment Failure†** | | | |
| Kanungu | 73% | 37% | - |
| Mubende | 42% | 13% | - |
| Kyenjojo | 58% | 22% | - |
| Kampala | 39% | 15% | 4% |
| Jinja | 49% | 14% | 6% |
| Tororo | 34% | 19% | 12% |
| Apac | 10% | 2% | 6% |

* Rescue therapy defined as quinine treatment given to a study subject when a treatment failure was identified based on results unadjusted by genotyping, and includes all early and late treatment failures

† Clinical treatment failure includes all early treatment failures and late treatment failures due to recrudescence after adjustment by genotyping (censoring new infections).

## 2.1.1 Revision of the antimalarial drug policy in Uganda

Available data from recently conducted efficacy studies were evaluated at a national consensus meeting in May 2004 to review Uganda's national antimalarial drug policy. Given substantial evidence that CQ+SP was failing, a decision was made to abandon this as the first-line regimen. Despite limited data on the comparative efficacy, safety, and cost-effectiveness of alternative regimens, there was urgent need to select a replacement regimen for first-line treatment, and only artemisinin-based combination therapies (ACTs) are being considered for first-line treatment. Although AQ+AS is an option, concern about the safety and tolerability of AQ, in addition to AQ resistance, may limit support for this combination. Coartemether, a co-formulated regimen that combines artemether, an artemisinin derivative, with the novel agent lumefantrine, is the likely replacement for first-line therapy, although data on this combination are very limited in Uganda. To facilitate rational drug policy decision-making, the investigation of alternative antimalarial regimens is essential.

## 2.2 Study drugs

### 2.2.1 Combination antimalarial therapy

Combination therapy has become the standard for the treatment of many infectious diseases. The advantages of combination therapy are improved efficacy and decreased selection of resistant organisms. Combination antimalarial therapy has already become standard in Southeast Asia, including Thailand where artesunate plus mefloquine is the standard regimen for falciparum malaria in areas with high-level drug resistance [4, 5]. Use of combination therapy, particularly ACT has also been strongly advocated in Africa [6] However, despite the substantial international support for ACTs, obstacles to widespread use of these regimens exist, including safety, cost, and drug availability.

### 2.2.2 Amodiaquine + artesunate (AQ+AS)

**Amodiaquine**

Amodiaquine (AQ) is very similar in structure to chloroquine (CQ), and the two drugs probably share mechanisms of action. Despite concerns about cross-resistance with CQ, AQ generally retains activity for the treatment of uncomplicated malaria in settings where CQ treatment failure is very common [7]. Use of AQ has been limited since the 1980’s due to concerns over toxicity, primarily hepatotoxicity and blood dyscrasias in individuals receiving long-term therapy for chemoprophylaxis [7]. However, AQ has remained available and inexpensive in Africa, and it has been fairly widely used as a replacement for CQ. Recent studies have suggested that AQ is, indeed, efficacious and safe when used for the treatment of uncomplicated malaria, even in areas of high-level CQ resistance [7-11]. In a study from Kampala, efficacy with AQ monotherapy has been shown to be markedly superior compared to previous studies with CQ alone in the same target population (14-day treatment failure rate 7% vs. 47%) [11, 12]. Based on data from multiple studies showing limited toxicity and marked improvement in efficacy over CQ, AQ is now increasingly advocated for use in the treatment of uncomplicated malaria in Africa.

**Artemisinin derivatives**

Artemisinins are a recently developed class of antimalarials that are natural products or semi-synthetic compounds derived from the plant *Artemesia annua* [13]. The artemisinins offer very rapid and potent treatment for malaria, and they benefit from a lack of known drug resistance. However, artemisinin derivatives are currently expensive, and because of their short half-life ideally should be given for extended courses or in combination with other drugs. Artemisinin derivatives given at high doses produce a selective neurotoxicity in laboratory animals, but this toxicity has not been observed in humans, and the drugs appear to be safe and well-tolerated.[14] Evidence of reproductive toxicity in animals treated with artemisinins in early pregnancy is of perhaps greater concern, and has led the WHO to recommend avoiding the use of artemisinin compounds in the first trimester.[15]

**Amodiaquine plus artesunate (AQ+AS)**

In recent comparative studies conducted in Kampala, Jinja, Tororo and Apac districts in Uganda, AQ+AS was well-tolerated and showed superior efficacy over CQ+SP. Compared to AQ+SP, AQ+AS had a lower risk of clinical treatment failure but a higher risk of new infection (UMSP, unpublished data and Staedke, in press) [3]. A multi-center study evaluating AQ+AS in Kenya, Senegal, and Gabon, which included 470 treatments, showed that the regimen was well-tolerated and provided excellent efficacy for uncomplicated malaria [16]. Three countries in Africa (Burundi, Gabon, and Zanzibar) have selected the combination of AQ+AS as first-line therapy [17].

### 2.2.3 Artemether plus lumefantrine (Coartemether)

Coartemether (Coartem) is an oral preparation containing the artemisinin derivative, artemether, and lumefantrine (previously known as benflumetol). As with other artemisinins, artemether is characterized by rapid antimalarial action, however, recrudescence is frequent when artemether is provided as a single agent, unless given for at least 5-7 days [18, 19]. Lumefantrine also has a high cure rate, but parasite and fever clearance is slower than with artemether [20]. The fact that coartemether combines an artemisinin derivative with a novel agent in a fixed dose regimen is an important advantage of this therapy. It is currently the only co-formulated antimalarial regimen and is included on the WHO Essential Drugs List [21]. However, coartemether is administered twice daily (a total of 6 doses over 3 days), and should ideally be taken with fatty food or liquid to maximize absorption, raising concerns about adherence.[22] In addition, the currently recommended 6 dose regimen has been little studied in Africa.[22] Coartemether has been selected as first-line therapy in South Africa (Kwazulu Natal), Zambia, and Comoros, and as second-line therapy for treatment of first-line failures in Cote d'Ivoire, Gabon, Mozambique, Senegal, and Zanzibar. [23]

## 2.3 Rationale

ACTs have been strongly advocated for use in Africa, but data on these regimens are currently limited. In recent UMSP studies, AQ+AS was safe and efficacious. However, compared to AQ+SP, the risk of recrudescence with AQ+AS was significantly lower at only one site (Kampala), while the risk of new infection with this regimen was significantly higher in 2 of 4 sites (Apac and Tororo) (UMSP, unpublished data and Staedke, in press) [3]. Coartem has been provisionally chosen as the replacement to CQ+SP as first-line therapy, but there is little data on the efficacy and safety of this regimen in Uganda, and its substantial cost (US$ 2.40 per adult treatment vs. US$ 1.30 for AQ+AS) [24] remains a significant obstacle. We are proposing to compare the efficacy, safety and tolerability of AQ+AS and Coartem for the treatment of uncomplicated falciparum malaria in Uganda. The data that is collected in this study will be made directly available to the Ugandan MoH to assist in drug policy decision-making.

# 3.0 STUDY AIM

To compare the efficacy, safety, and tolerability of AQ+AS and coartemether for the treatment of uncomplicated falciparum malaria in Uganda.

# 4.0 STUDY DESIGN

## 4.1 Overall study design

The study will be a randomised, single-blinded trial designed according to 2003 World Health Organization (WHO) guidelines for assessment of therapeutic efficacy of antimalarial agents in areas of low, moderate and intense transmission [25] with slight modifications. The target population includes residents of the catchment areas of the four clinical sites in Uganda. The available population includes residents aged 6 months and older who present to the study clinics with symptoms suggestive of malaria and who have a positive screening thick blood smear. Subjects who meet the selection criteria will be randomized to treatment with one of the two study regimens and will be followed for 28 days. Repeat evaluations will be performed on days 1, 2, 3, 7, 14, 21, and 28 (and any unscheduled day) and will include assessment for the occurrence of adverse events. Treatment efficacy outcomes will be assessed using WHO outcome classification criteria (Appendix 7).

## 4.2 Study outcome and assessment

### 4.2.1 Classification of treatment outcome

Response to treatment will be classified according the recently proposed WHO classification system, and will include adequate clinical and parasitological response (ACPR), early treatment failure (ETF), late clinical failure (LCF), and late parasitological failure (LPF), for purposes of data reporting (Appendix 3). [26] In the final analysis, treatment outcomes will be dichotomized based on the following definitions:

- Clinical rescue therapy = ETF + LCF
- Parasitological rescue therapy = ETF + LCF + LPF.

All ETFs will be considered true treatment failures. For all LCFs and LPFs, molecular genotyping will be used to distinguish recrudescence (true treatment failure) from new infection (see section 11.3).

- Clinical treatment failure = All ETFs + LCFs due to recrudescence
- Parasitological treatment failure = All ETFs + LCFs/LPFs due to recrudescence

### 4.2.2 Primary outcome

Primary outcome will be based on the risk of clinical rescue therapy. Pairwise comparisons between regimens will be made based on a per-protocol analysis.

### 4.2.3 Secondary outcomes

1. Risk of clinical treatment failure
2. Risk of parasitological rescue therapy
3. Risk parasitological treatment failure
4. Risk of fever during the first 3 days of follow-up: presence or absence of objective fever (axillary temperature > 37.5C) or patient report of fever on days 1, 2, 3
5. Risk of parasitemia on follow-up days 2 and 3: proportion of positive vs. negative thick blood smears on day 2 and day 3
6. Change in mean haemoglobin from day 0 to 28 or day of repeat therapy
7. Proportion of subjects lacking gametocytes on day 0 with gametocytaemia on any follow-up day
8. Risk of serious adverse events: proportion of patients experiencing any serious adverse event in each treatment group during the 28-day follow-up period, excluding treatment failures
9. Risk of adverse events of moderate or greater severity, at least possibly related to the study medications, excluding treatment failures.

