# 7.0 FOLLOW-UP EVALUATION AND PROCEDURES

## 7.1 Follow-up schedule

Patients will be asked to return to the clinic for follow-up on days 1, 2, 3, 7, 14, 21, 28, and any unscheduled day that they feel ill. All patients will be reimbursed the cost of their transport to and from the clinic. At enrolment, details about the location of the patient’s residence will be obtained and if a subject does not return for a scheduled clinic follow-up appointment, the study personnel shall visit them at home. Patients who return on day 1 and fail to fulfil the criteria of *P. falciparum* mono-infection with a parasite density of > 2000 parasites/ul and < 200,000 parasites/ul will be excluded from further study and referred to OPD for management. At each repeat visit, temperature will be measured and a focused physical examination will be performed. A finger prick blood sample will be obtained on days 2, 3, 7, 14, 21 and 28 (and any extra day) to repeat thick blood smears and to save on filter paper. Haemoglobin will be re-evaluated on day 28 or at the time of clinical treatment failure.

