## 7.2 Classification of treatment outcome and management of treatment failure

Patients will be followed for 28 days and will have treatment outcomes assessed according to the WHO 2003 guidelines (Appendix 7). Patients who require clinical rescue therapy (ETF, LCF, or LPF) will be treated with quinine 10 mg/kg orally three times a day for 7 days. Any patient who is diagnosed with severe malaria or danger signs during follow-up, will be referred for appropriate treatment with parenteral quinine at the local facility or hospital. Patients not admitted to the hospital will receive oral quinine to complete a 7-day course of therapy. If a patient requires clinical rescue therapy, formal study follow-up will end, and the patient will be followed up at the discretion of the study physician. Haemoglobin measurement will be repeated on the day the patient receives clinical rescue therapy.

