# APPENDIX 7. CLASSIFICATION OF RESPONSE TO TREATMENT

**Early Treatment Failure (ETF)**

| **ETF**   - Development of danger signs or severe malaria on Day 1, Day 2 or Day 3 in the presence of parasitemia - Parasitaemia on day 2 higher than Day 0 count irrespective of axillary temperature. - Parasitaemia on Day 3 with axillary temperature > 37.5 0C - Parasitaemia on Day 3 > 25% of count on Day 0. - Severe AE requiring change in treatment Days 0 - 2 |
| --- |

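### The Day 3 parasitaemia proportion omits children rescued for parasitaemic early failure on Day 1 or 2, so an arm with more such rescues looks faster to clear than it is

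*Protocol*

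**What the plan says.** Secondary outcome 5 in section 4.2.3 is the risk of parasitaemia on Days 2 and 3, measured as the "proportion of positive vs. negative thick blood smears on day 2 and day 3". Section 7.1 schedules the samples: "A finger prick blood sample will be obtained on days 2, 3, 7, 14, 21 and 28". Table 4 agrees and shows no thick smear on Day 1.

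Appendix 7 lets an ETF be declared before the Day 3 smear in three ways:

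- The first is clinical worsening: "Development of danger signs or severe malaria on Day 1, Day 2 or Day 3 in the presence of parasitemia".
- The second is a rising count, whether or not the child is febrile: "Parasitaemia on day 2 higher than Day 0 count irrespective of axillary temperature".
- The third is not parasitological in itself: "Severe AE requiring change in treatment Days 0 - 2".

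Section 7.2 sends these children to rescue: "Patients who require clinical rescue therapy (ETF, LCF, or LPF) will be treated with quinine". It then says: "If a patient requires clinical rescue therapy, formal study follow-up will end". Any later contact is left to the study physician.

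Section 9.2 analyses efficacy per protocol, in patients who have a treatment outcome. ETF is such an outcome, and it is not among the reasons for exclusion in section 7.3, so these children remain in the efficacy set.

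**The concern.** A child rescued on Day 1 or 2 is in the analysis set but has no scheduled Day 3 smear, and so counts as neither positive nor negative. The smear is missing because of how the child responded to treatment. Most of these children were parasitaemic when they were rescued, and leaving them out lowers the Day 3 proportion. If the arms differ in early rescue, the proportion is lowered more in the arm with more of it, and the comparison of early parasite clearance shifts in that arm's favour.

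Other items in the same list say what happens to failed or rescued children. Item 6 takes haemoglobin at the day of repeat therapy, and items 8 and 9 exclude treatment failures. Item 5 has no such rule.

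**Working it through.** **Inputs.** The protocol gives no ETF rate and no expected Day 3 positivity. Table 1 does not help, because its rescue figures pool early and late failures. There is thus no figure for this outcome to reproduce, and e and p below are assumptions. The planned size is 200 per arm per site with 10% loss (section 9.1): 200 × 0.9 = 180 evaluable per arm at one site and 4 × 180 = 720 over four sites. The detectable difference of about 15% in section 9.1 concerns the primary outcome and is not in question.

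**Formula.** Let e be the share of an arm rescued on Day 1–2 with parasitaemia, and p the share not cleared by Day 3 when those children count as not cleared. Then:

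- proportion on smears taken = (p − e)/(1 − e)
- understatement = p − (p − e)/(1 − e) = e(1 − p)/(1 − e)

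The understatement rises with e. For p = 10% it is 0.01 × 0.90/0.99 = 0.91 points at e = 1%, and 0.03 × 0.90/0.97 = 2.78 points at e = 3%. The difference, 1.87 points, is the false gap.

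**Equal full rate p in both arms (assumed values).**

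| p | e, arm A vs B | Smears taken, A vs B | False gap (points) |
|---|---|---|---|
| 2% | 0% vs 1% | 2.00% vs 1.01% | 0.99 |
| 5% | 0% vs 1% | 5.00% vs 4.04% | 0.96 |
| 5% | 1% vs 3% | 4.04% vs 2.06% | 1.98 |
| 10% | 0% vs 1% | 10.00% vs 9.09% | 0.91 |
| 10% | 1% vs 3% | 9.09% vs 7.22% | 1.87 |
| 20% | 0% vs 1% | 20.00% vs 19.19% | 0.81 |

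Per 1-point difference in e, the false gap is about 0.8 to 1.0 point.

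**Effect on a test.** This uses a pooled two-proportion normal test at two-sided 0.05 with the full rates truly equal. For p = 10% and e = 1% vs 3%, the chance of a significant result is 9.8% at 180 per arm and 25% at 720. For p = 5% and the same e it is 18.9% and 57.9%. The second case is demanding: early rescues would make up 3 of the 5 points of non-clearance in arm B.

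**Equal positivity among children not rescued.** The full rate is e + (1 − e)r, where r is the positivity among children with a smear. With r = 5% and e = 1% vs 3%, the smears show a tie at 5%, while the full rates are 0.01 + 0.99 × 0.05 = 5.95% and 0.03 + 0.97 × 0.05 = 7.85%.

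**Ranking preserved.** With e = 1% vs 3% and r = 3% vs 8%, smears show 3% vs 8%. The full rates are 0.01 + 0.99 × 0.03 = 3.97% and 0.03 + 0.97 × 0.08 = 10.76%. The order is the same, with a smaller gap on smears.

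**Equal early rescue.** With the same e in both arms, the observed difference is the full difference divided by 1 − e. For e = 2% and p = 5% vs 10%, that is 5/0.98 = 5.10 points instead of 5, which is immaterial.

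**The case against.** **The statistical analysis plan may settle it.** Rules for missing smears on a secondary outcome often sit there, and that document is not shown. This would carry more weight if 4.2.3 only named the outcome. It also fixes the measure, as positive against negative smears, and that measure loses children for a reason tied to the outcome.

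**The early failures are visible elsewhere.** This is correct. A child who fails on the Day 2 count is by definition positive on Day 2 and counts in that half of outcome 5. A child who fails on Day 3 has a Day 3 smear. Under section 4.2.1 every ETF counts in the primary outcome and in secondary outcomes 1 to 3. What remains is the Day 3 half of outcome 5, plus any Day 1 rescues missing from Day 2.

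**A discretionary smear could exist.** Section 7.2 does not forbid one. But none is scheduled, and a smear after quinine would not measure the study drug.

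**The differences may be small.** Both regimens contain an artemisinin derivative, a class that the protocol describes as very rapid and potent. Nothing in it points to a large difference between arms in Day 1–2 failure. Even full rates of 4.94% vs 3.49% (e = 2.0% vs 0.5%, r = 3%) would give z of about 1.4 at 720 per arm. This stands, and it keeps the point minor.

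**Stronger readings.** A reader might infer that the arm with more early failures will appear better than the other arm, against the truth. That does not follow: it appears better than it is, and the worked cases include a tie and a preserved ranking. A reader might also take all rescued children to be the poorest parasitological responders. A severe adverse event on Days 0–2 also makes an ETF, and danger signs with any parasitaemia suffice, so that is not supported.

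**Conclusion.** The point holds as a minor one. As defined, the Day 3 proportion understates non-clearance in any arm that has parasitaemic ETFs on Day 1 or 2, and does so more in the arm with more of them. The direction follows from the definition in 4.2.3 together with section 7.2 and Appendix 7. It assumes that a child rescued with parasitaemia should count as not cleared by the study drug.

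The size cannot be derived from the protocol. The figure of 0.8 to 1.0 point per 1-point difference in early rescue rests on assumed full rates of 2% to 20%, equal between arms. If early rescue and true positivity are similar in the two arms, the difference is not materially biased. The primary outcome and the sample size are untouched.

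**What to change.** In section 4.2.3, item 5:

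- Define Day 3 parasitaemia among children who have a Day 3 smear or had a parasitaemic ETF before it, and count those ETFs as not cleared.
- Treat parasitaemic ETFs on Day 1 the same way for the Day 2 proportion.
- Leave out ETFs due only to a severe adverse event, and children lost or withdrawn before the smear, and report their numbers by arm. A denominator of all treated children would count those lost as not positive and favour the arm with more loss.
- Report the smear-only proportion alongside.

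Do not carry the rule over to the fever outcome (item 4). The Day 2 count criterion applies whatever the temperature, so a rescued child without fever would be labelled febrile.

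The cost is a short addition to the text, with no new data and no change to patient care. The downside is that Day 3 parasitaemia becomes a composite with early malaria rescue, which is why the smear-only figure should stay beside it.
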